
### Estimation of hospital operational costs

Data collected for hospital indirect cost components – training, communications and supplies – are annual and relate to all infants assessed for PSBI during that year. For each site, expenses for training, communications and supplies will be added across facilities. The number of infants assessed during a year at a hospital will be estimated based on the total number of infants assessed over the entire study period and proportionally for 12 months. The sum of expenditures for each component will be weighted by the number of SYI assessed at each hospital for PSBI during the year to obtain the weighted expense per SYI at each site.Inpatient bed costs are shared costs across all infants and children admitted to newborn intensive care units and paediatric wards for shared items such as non-consumables, utilities, laundry, security, administration and other departmental expenses. The costs per admitted child will be estimated by dividing the total annual administrative expenditures (exclusive of staff costs, medicines, and consumables costs for enrolled SYI) of the paediatric and newborn intensive care units by the total number of children admitted in that year. These will be adjusted proportionately based on the average length of stay for enrolled SYI with PSBI relative to other SYI admitted during the year. We assume there are no inpatient bed costs for the intervention arm (outpatient) under RCT1 and for the 5-day ambulatory treatment in RCT2.Hospital transport/ambulance costs may be incurred for some patients brought to the hospital by public ambulance. Since it is difficult to obtain the data from the hospital database for each SYI enrolled, an indirect estimation method will be used. Household survey data will be used to determine the proportion of SYI who report using free public transport under different RCT treatment arms. Each site will calculate the average cost per trip based on the average distance to the hospital and the cost per km or mile. The cost per km depends on drivers' salaries, fuel costs for the average distance to hospitals in the study area, and vehicle maintenance costs at the site. Multiplying the average costs by the estimated number of SYI using public transport under each arm will provide an estimate of transport costs incurred at the hospital level.

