**Conclusions:**

This CE framework will evaluate thresholds for new PSBI treatment strategies in YIs, integrating health system and household perspectives. It will seek to identify safe, cost-effective approaches to reduce economic burdens, inform national budgetary impact, and potentially prompt WHO guideline revisions to improve infant care in low-resource settings globally.

In 2024, around 2.3 million neonatal deaths occurred worldwide, accounting for 47% of all under-five deaths [1], with infections responsible for up to 37% of these deaths in South Asia and sub-Saharan Africa [2]. The World Health Organization (WHO) recommends hospital referral for inpatient injectable therapy for at least seven days with supportive care, if needed, for young infants (YIs) (0–59 days old) with any sign of possible serious bacterial infection (PSBI) [3,4]. However, in resource-limited settings, a large proportion of the families of YI with PSBI refuse hospital referral due to several barriers, such as distance to the health facility, cost of hospitalisation, daily wage loss during the hospitalisation period and cultural constraints resulting in newborn deaths [5–8].

To address these barriers, several clinical trials [5–12] and research have been conducted in Africa and Asia to assess the feasibility of implementation [13] of the WHO PSBI management guidelines [14] and to establish that YI with clinically severe infection (CSI) and pneumonia (subclassification of PSBI) treated with simplified outpatient antibiotic regimens are effective. Pooled analyses of three trials from Africa and Asia reported that a simplified treatment regimen using oral amoxicillin with gentamicin had better outcomes compared to other regimens in ambulatory settings [15]. Secondary analysis of the African Neonatal Sepsis Trial further highlighted that infants with signs of CSI had higher mortality rates when treated in a hospital compared to outpatient treatment. This secondary analysis further divided these signs into low- or moderate signs based on the case fatality ratio associated with each CSI sign [16].

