### Costs framework

The cost will be assessed from both the hospital and household perspectives. From the hospital perspective, medical treatment costs will be determined at each study hospital across all sites in both the intervention and control arms (**Table 1**, **Table 2**). Additionally, the household's costs will be separated into medical and non-medical costs. The hospital's indirect operational costs and households' opportunity costs in terms of wage loss will also be estimated. The costs will be weighted by infant days for each hospital, separately for the control and intervention arms, to obtain site-specific average costs for each item. To generate combined estimates, we will pool site-specific average costs across all sites to produce a single multi-country mean cost for inpatient and outpatient management, respectively.

**Table 1 T1:** Framework for provider costs under RCT1: outpatient versus inpatient management of young infants (0–59 days) with low-mortality-risk PSBI signs

Cost category	Intervention arm: outpatient treatment	Control arm: inpatient treatment
Place of treatment	Outpatient/ambulatory care	Hospital inpatient care
Antibiotic regimen	Injectable gentamicin once daily for 2 days plus oral amoxicillin twice daily for 7 days	Injectable ampicillin (2–4 times daily depending on age) plus injectable gentamicin once daily for 7 days
Staff costs	Outpatient assessment, counselling, injections preparation (canula), gentamicin administration, follow-up visits	Inpatient assessment, nursing care, injections preparation (canula) + administration, monitoring and supportive care
Medicine costs	Gentamicin and oral amoxicillin	Ampicillin and gentamicin
Consumables	Syringes, needles, cotton swabs, gloves, cannula, spirit	Syringes, needles, intravenous supplies, cotton swabs, gloves, cannula, spirit
Inpatient bed costs	Not applicable	Included for the duration of hospitalisation. Captures costs in the paediatric wards, such as costs of non- consumables, utilities, security, and laundry
Operational and indirect costs	Training, supervision, communication, administration and programme support	Training, supervision, communication, administration and programme support
Weighting approach for pooled analysis	Infant-days (number of infants treated and days each medicine or consumable is used)	Infant-days (number of infants treated and days each medicine or consumable is used)

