Coverage of sick YIs (SYI) assessed, enrolled and treated under both RCT1 and RCT2 for control and intervention.Data on two outcome variables for all SYI covered under different treatment arms. Well-trained independent outcome assessor visits all enrolled cases on days two (only for RCT1), four, eight, and 15 after the initiation of treatment to assess the study outcomes in both intervention and control arms.Average annual salaries of nurses, paediatricians, medical officers and any other staff supporting treatment. To calculate staff costs per minute, data will be collected on the average number of days in a month and the average number of hours in a day that staff work.Staff time will be considered only for activities that are linked to hospital staff and not those linked to research staff, such as outcome assessment or treatment documentation (**Table 1**, **Table 2**). The activities for the staff time will be based on a pre-defined implementation strategy [21,22].Data will be collected for SYI that receive at least 80% of the treatment (recommended treatment) and those who receive <80% of seven-day (<5.5 days) treatment (partial treatment). The latter occurs due to a treatment failure, a change in treatment, readmission, left voluntarily, or death. For the recommended treatment, we will collect costs for the seven-day treatment period following the initial assessment, across both study arms and both trials. For partial treatment, medical costs will be calculated for an average treatment period of three days in RCT1 after the initial assessment, and for two days in RCT2 in both inpatient and outpatient arms after randomisation. Costs for enrolled SYI will be weighted by the proportion of participants receiving 80% recommended treatment and those receiving partial treatment, with weights set to SYI for each group. This prevents any child randomised and enrolled from being missed. Costs due to complications, changes in treatment, and/or readmission are outside the seven-day recommended treatment window in both study arms of both trials and will not be collected.Data on staff time per visit for an activity and the number of visits undertaken for each activity during the recommended treatment period will be collected by interviewing at least 3–5 staff of each type at each hospital.The staff time for all visits during the treatment period will be weighted by the number of days an infant receives the activity and the number of YI receiving the activity (defined as weighted by infant days). For the first activity assessment on presentation at the hospital, the number of SYI will be all enrolled for a given treatment, whether partial or recommended. For all other activities, SYI who receive 80% recommended treatment will be considered to have received seven days of treatment, and those receiving partial treatment for an average of three days to calculate the costs for those enrolled.The average exchange rate used to convert all the cost estimates in local currency into USD will be for 2024, the period for which the salaries of providers, prices and household costs will be reported. It will ensure consistency, and inflation rate adjustments will not be needed for cost calculations. The recommended treatment period will be seven days for inpatient treatment in the control arm and seven days for outpatient treatment in the intervention arm for RCT1. For RCT2, the average length of inpatient treatment is 48–72 hours, prior to a negative CRP laboratory test. In RCT2, the control group after randomisation will continue receiving inpatient care for five days, while the intervention group will be discharged from the hospital on oral amoxicillin for five days to be taken at home. Both arms will share the initial hospitalisation costs during the first two days in RCT2, including CRP test costs (including staff time, kits, and laboratory costs).The data on quantities used of injection gentamicin, injection ampicillin and oral amoxicillin will be as per the recommended treatment and partial treatment per SYI for each treatment arm under each RCT.The number of SYI receiving specific medicines and consumables for each arm under both RCTs will be calculated based on the numbers receiving recommended treatment and those receiving partial treatment.Information on types and quantities of consumables required with each medicine will be collected separately for each hospital and each arm under both RCTs. The cost of medicines and consumables will be charged per size in which they are dispensed. Medicine dosage varies with the weight of the YI [21,22]. Price will be taken for full strength, and the rest will be marked as wastage. Price data will be taken from the hospital's pharmaceutical department (if available); otherwise, the market price or the WHO price will be used.Data on annual financial expenditures and admissions in the newborn intensive care units or paediatric wards where YI with PSBI are treated as inpatients at the hospital will be collected and allocated based on patient days to calculate the inpatient bed costs/ SYI treated as an inpatient. These expenditures include administration, utilities, laundry, security, data management, internet, non-consumables and other costs in the hospital inpatient ward.Hospital ambulance to transport enrolled SYI under a specific treatment arm is a cost to the hospital. It is difficult to get this information separately for each enrolled SYI under different treatment arms from the hospital data. Indirect estimation based on the average trip cost and the number of SYI using free public ambulances, estimated from household data for each treatment arm in RCT1 and RCT2, will be used.Hospital data will also be collected for operational costs, which help to strengthen the assessment, identification, and treatment of SYI with PSBI. These include training, supplies, and communication. The total costs under these three will be estimated per SYI assessed. Staff training costs include the costs of development of training material and training cost per staff per day based on the per diems, honorarium for trainers, venue and refreshment costs. Total training costs will be calculated for all staff who were used to assess and treat SYI and will be estimated per SYI assessed. Training costs for research staff for outcome assessment or data collection will not be collected or included. Price and quantities of supplies used during the assessment, such as timers, thermometers and weighing scales, will be prorated for PSBI assessed. Communication costs, include job aids or educational material, and the cost of videos developed and played at the hospitals for educating the mothers about the danger signs. Data will be collected on item quantities and prices from hospitals to assess total costs and costs per SYI assessed.

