### CEA

CE will be evaluated by estimating the ICER, defined as the difference in mean costs between the intervention and control arms divided by the difference in effectiveness between the two arms: ICER = (C_1_ − C_2_) / (E_1_ − E_2_), where C_1_ are the average costs for the intervention group; C_2_ are the average costs for the control group; E_1_ is the mean effectiveness measure for the intervention group, and E_2_ is the mean effectiveness measure for the control group. We will use societal costs – hospitals and households’ – medical costs (staff time, medicines, consumables); hospital inpatient bed cost, operational costs and households’ non-medical costs (transport, food and wage loss) for ICER calculations for all randomised SYI in both arms. We will also report ICER from only the provider/payer perspective using only medical costs for all enrolled SYI and those receiving at least 80% of the recommended seven-day treatment as a sensitivity analysis [27].

For RCT2, while the baseline costs will be presented for both pre- and post-randomisation for both study arms, the costs for ICER calculations will be compared only post-randomisation.

For each RCT, cost measures will be evaluated in both the control and intervention arms for all enrolled infants who receive either the full seven-day treatment or partial treatment. Effectiveness will be assessed in the same population based on clinical outcomes recorded on days two (for RCT1), four, eight, and 15 following treatment initiation. The ICER will be calculated for each RCT to assess whether the intervention is more cost-effective than the control.

There can be 4 case scenarios for ICER (**Figure 2**):

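### Inpatient bed cost is averaged over all admitted children but scaled by stay relative to other sick young infants only, which conflicts with the patient-day allocation stated elsewhere

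*Protocol article*

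**What the plan says.** The section *Estimation of hospital operational costs* builds the bed cost in two steps.

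- **Average.** The cost pool is described thus: "Inpatient bed costs are shared costs across all infants and children admitted to newborn intensive care units and paediatric wards". The annual overhead of these units is divided "by the total number of children admitted in that year".
- **Scaling.** The resulting cost per admission is then "adjusted proportionately based on the average length of stay for enrolled SYI with PSBI relative to other SYI admitted during the year".

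The *Hospital data* section describes the same expenditure as "allocated based on patient days to calculate the inpatient bed costs/ SYI treated as an inpatient".

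The introduction defines the population as "young infants (YIs) (0–59 days old", so SYI are only some of the children admitted to a paediatric ward.

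On where the cost falls, *Estimation of hospital operational costs* states: "We assume there are no inpatient bed costs for the intervention arm (outpatient) under RCT1 and for the 5-day ambulatory treatment in RCT2". The *CEA* section includes "hospital inpatient bed cost, operational costs and households’ non-medical costs (transport, food and wage loss) for ICER calculations", and for RCT2 it compares only costs that arise after randomisation.

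**The concern.** A cost per average admission becomes a cost for a particular stay when it is multiplied by that stay over the mean stay of the children who were averaged. Here the average is over all admitted children, but the reference stay is that of other SYI. The result is neither a patient-day allocation nor any other allocation that adds back to the expenditure, unless the two groups happen to have the same mean stay. An analyst cannot follow both this section and *Hospital data* when the means differ.

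The error would fall on one arm. The RCT1 outpatient arm carries no bed cost. In RCT2 the shared first days are outside the ICER and the five ambulatory days carry none. Nothing cancels, so an error in the bed cost shifts Δc by the same absolute amount. The INB, which the *CEA* section defines as λΔe − Δc, shifts by that amount too. The planned confidence interval for the INB rests on variation between sites, so it would not reveal a bias that the sites share.

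**Working it through.** The article states no bed cost, expenditure, admission count or comparator stay, so there is no figure to reproduce. The check is algebraic, followed by illustrations in which every number is assumed.

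**Symbols.** E = annual overhead of the units; N = all children admitted in the year; L_enr, L_otherSYI and L_all = mean stay of enrolled SYI, of other SYI, and of all admitted children.

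**Rule in *Estimation of hospital operational costs*:** (E / N) × (L_enr / L_otherSYI).

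**Rule in *Hospital data* (patient days):** E × L_enr / (N × L_all) = (E / N) × (L_enr / L_all).

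**Ratio of the first to the second:** L_all / L_otherSYI. L_enr cancels, so the same factor applies to a full stay, a partial stay, or the RCT2 days after randomisation.

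**Direct illustrations of the factor**

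- L_all 5 days, L_otherSYI 7 days: 5 / 7 = 0.71.
- L_all 6 days, L_otherSYI 5 days: 6 / 5 = 1.20.

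**Worked example.** Assume E = 100,000 and N = 1,000, made up of 50 enrolled SYI staying 7 days, 450 other SYI and 500 older children. Then E / N = 100.

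| Assumed stay: other SYI / older children | Patient-days | L_all | As written | Patient-day rule | Ratio |
|---|---|---|---|---|---|
| 7 / 4 | 350 + 3,150 + 2,000 = 5,500 | 5.50 | 100 × 7/7 = 100.0 | 100 × 7/5.50 = 127.3 | 0.786 |
| 4 / 7 | 350 + 1,800 + 3,500 = 5,650 | 5.65 | 100 × 7/4 = 175.0 | 100 × 7/5.65 = 123.9 | 1.41 |
| 7 / 7 | 350 + 3,150 + 3,500 = 7,000 | 7.00 | 100 × 7/7 = 100.0 | 100 × 7/7 = 100.0 | 1.00 |

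In the first row the RCT1 saving per control infant treated for 7 days is understated by 127.3 − 100.0 = 27.3. For five days in RCT2 the figures are 100.0 × 5/7 = 71.4 as written against 127.3 × 5/7 = 90.9, which is the same ratio.

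**Range.** With the same admission counts, other SYI staying 3 to 10 days and older children 3 to 7 days, the factor ran from 0.64 to 1.73. With stays fixed at 7 days (other SYI) and 4 days (older children), and other SYI making up 20%, 50% or 80% of the 950 admissions not enrolled, it was 0.67, 0.80 and 0.92.

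**Direction.** The factor is below 1 (bed cost and saving understated) when other SYI stay longer than the mean of all admissions. It is above 1 when they stay less.

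**The case against.** The strongest reply is that the comparator is loosely worded. Multiplying a cost per admission by a relative length of stay is a common way to reach a patient-day allocation from admission counts, and expenditure and admissions are what *Hospital data* says will be collected. If other SYI simply means the other admitted children, the two sections describe nearly one rule. Over the same assumed grid the factor is then 0.99 to 1.07, because only the small enrolled group is left out of the comparator. This reading is possible. However, the section speaks of infants and children, or of children admitted, when it means everyone, and changes to SYI only for the comparator. As written it instructs something else, and the wording needs correcting on either reading.

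Three stronger readings are tempting, and the article does not support them.

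- **That the bed cost is the main cost difference between arms.** No amounts are given. Table 1 also has the arms differing in nursing, monitoring, medicines and consumables, and household costs may differ too.
- **That pooling newborn intensive care with the paediatric ward is an error.** Table 1 says of the bed cost: "Captures costs in the paediatric wards". But *Hospital data*, *Estimation of hospital operational costs* and *Site-wise and combined analysis plan* all name newborn units as well and expect infants in both settings. The table's shorter wording is at most a point to tidy.
- **That each infant's recorded days by ward are required.** The average inpatient days per arm are enough to make the two rules agree.

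**Conclusion.** The concern holds as an internal contradiction with a one-sided effect. The bed-cost rule averages over one group and scales by another, and it differs from the patient-day allocation by the factor L_all / L_otherSYI. This follows from the text alone.

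A reader might infer that the cost difference is misstated, or that the saving is understated. Neither can be shown. Without lengths of stay the size and direction are unknown, and the factor is exactly 1 if the two mean stays are equal. The values 0.71 and 1.20, and the wider range of 0.64 to 1.73, rest entirely on assumed stays and case mix. What can be said is that the bed cost may be biased by this factor, and that any such bias passes undiluted into Δc, the ICER and the INB. The point should be corrected before analysis.

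**What to change.** State one rule in both sections. Either of these wordings achieves it, and they are algebraically the same:

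- in *Estimation of hospital operational costs*, replace the comparison with other SYI by a comparison with the mean stay of all children counted in the admissions denominator; or
- define bed cost as annual expenditure divided by annual patient-days, multiplied by the average inpatient days of enrolled SYI in that arm (for the RCT2 ICER, the days after randomisation).

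This is a change of formula in the analysis. The rule as written already needs a comparator stay, so the extra requirement is that it covers all admissions. *Hospital data* lists annual expenditure and admissions, not patient-days, so some of the 31 hospitals may have to supply a mean stay or patient-days for all admissions. Because *Framework for analysis* gives 19 August 2024 as the end of data collection, these would be retrieved from hospital records.

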### Data collection

#### Hospital data

Provider data will be gathered using standardised hospital/provider questionnaires for both control and intervention arms in RCT1 and RCT2. Data will be collected from 31 hospitals (30 in RCT1 and 29 in RCT2) from all seven sites (four hospitals in Bangladesh, five in Ethiopia, six in India Himachal Pradesh and the National Capital region, six in India Uttar Pradesh, three in Nigeria, five in Pakistan, and two in Tanzania) where YI are enrolled for treatment under RCT1 and/or RCT2.

Provider data for CEA will include the following variables:

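### Ward running costs are estimated only for inpatient stays, with no counterpart for outpatient attendances, which tilts the incremental cost modestly towards the intervention arms

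*Protocol article*

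**What the plan says.** The inpatient bed cost is built from ward running costs. Estimation of hospital operational costs describes "shared items such as non-consumables, utilities, laundry, security, administration and other departmental expenses", taken from the paediatric and newborn intensive care units. The Hospital data section gives the fuller list: "These expenditures include administration, utilities, laundry, security, data management, internet, non-consumables and other costs in the hospital inpatient ward". In Table 1 the control-arm cell reads "Captures costs in the paediatric wards, such as costs of non- consumables, utilities, security, and laundry", and the corresponding cell for the RCT1 intervention arm is marked as not applying. The rule for outpatient care is explicit: "We assume there are no inpatient bed costs for the intervention arm (outpatient) under RCT1 and for the 5-day ambulatory treatment in RCT2".

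Outpatient care still draws on provider resources. Table 1 lists staff time in the RCT1 intervention arm for "Outpatient assessment, counselling, injections preparation (canula), gentamicin administration, follow-up visits", and Table 2 includes outpatient follow-up in the RCT2 intervention arm. Cost data for both arms come from the study hospitals: "Provider data will be gathered using standardised hospital/provider questionnaires for both control and intervention arms in RCT1 and RCT2".

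On indirect costs common to both arms, the article gives two lists. The operational rows of Tables 1 and 2 read "Training, supervision, communication, administration and programme support" in every arm. The Hospital data section says of operational costs: "These include training, supplies, and communication. The total costs under these three will be estimated per SYI assessed". Estimation of hospital operational costs repeats the same three items.

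**The concern.** An infant who returns for an injection or a review uses space, power, security, records and administration. The plan costs the staff, medicines and consumables of that contact but none of its running costs, while the comparator's running costs are charged for each day of stay. A whole class of cost is thus measured in one arm and has no line in the other.

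The items that do reach both arms cannot correct this. Training, supplies and communication are averaged over infants assessed, so at a given site each arm receives the same amount per infant and the difference is nil. The tables suggest that administration and supervision are also costed in both arms. The estimation text never computes them as operational costs, and it places administration inside the inpatient bed cost.

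The stake is the incremental cost, and lower cost is the advantage expected of both interventions (Hypothesis/objective). The bed cost enters the ICER and the INB directly (CEA section). The INB interval is built from variation between sites, so an omission that pushes every site the same way moves its centre without being reflected in its width. The sensitivity analysis named in the CEA section changes perspective and population, not overhead. Strengths and limitations does not mention the asymmetry.

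**Working it through.** The article states no unit cost, outpatient visit count or overhead ratio, so there is no planned figure to reproduce. The check has two parts: which costs reach which arm, and how large the missing item could be.

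**Which costs reach which arm**

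| Item | Inpatient care | Outpatient care | Source |
|---|---|---|---|
| Staff time, medicines, consumables | costed | costed | Tables 1 and 2 |
| Training, supplies, communication | per infant assessed | same amount per infant assessed | Hospital data; Estimation of hospital operational costs |
| Utilities, security, laundry, data management, internet, non-consumables | bed cost | no item | same sections |
| Administration | bed cost; also in the tables' operational row | tables' operational row only, not computed | Tables 1 and 2 against the same sections |
| Supervision, programme support | listed, not computed | listed, not computed | Tables 1 and 2 |

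**Size of the missing item**

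Inputs from the article: seven inpatient days for a full course in the RCT1 control arm; five post-randomisation inpatient days in the RCT2 control arm, with RCT2 costs compared only after randomisation; INB = λΔe − Δc, with Δc = C1 − C2.

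Assumed inputs: *v*, the distinct outpatient attendances in the intervention arm that have no counterpart in the control arm; and *f*, the running cost of one attendance as a fraction of *b*, the ward running cost per bed-day.

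- Incremental running cost as planned: −7b in RCT1 and −5b in RCT2.
- With outpatient running cost included: −(7 − vf)b and −(5 − vf)b.
- Overstatement as a share of the planned bed-cost saving: vf/7 and vf/5.
- Effect on the decision measures: Δc rises by vfb and INB falls by the same vfb.

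RCT1, v = 1 to 4 and f = 0.10 to 0.25:
- low: 1 × 0.10 = 0.1 bed-days; 0.1/7 = 1.4%
- high: 4 × 0.25 = 1.0 bed-day; 1.0/7 = 14.3%

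RCT2, v = 0 to 2 and f = 0.10 to 0.30:
- low: 0 bed-days; 0%
- high: 2 × 0.30 = 0.6 bed-days; 0.6/5 = 12%
- with f capped at 0.25 as in RCT1: 2 × 0.25 = 0.5; 0.5/5 = 10%

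**Could the sign reverse?** That needs vf above 7 in RCT1 or above 5 in RCT2. At f = 0.25 this means more than 7/0.25 = 28 attendances in RCT1; at f = 0.30, more than 5/0.30 = 16.7 in RCT2. Neither is plausible within a seven-day course or five days of oral treatment at home.

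These percentages refer to the bed-cost component alone. The share of total incremental societal cost is not derivable, because staff, medicines, consumables, transport, food and wage loss also contribute.

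**The case against.** The strongest reply is that the plan does nothing unusual. The pool is ward expenditure, it includes plainly bed-linked items such as laundry, and charging it to infants on the ward is ordinary allocation. The nil assumption is true by definition for an infant not in a bed. This stands: the sentence itself is not an error, and the defect is the missing outpatient item.

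A reader might infer that all facility overhead falls on inpatients and that outpatient overhead is set to zero throughout. The documents do not support that. Training, supplies and communication reach both arms, and Tables 1 and 2 list administration and programme support for both. The tables and the text disagree, but the disagreement does not prove a planned zero.

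A reader might also infer that the whole overhead of outpatient care enters the ICER uncancelled. It does not. Assessment on presentation applies to every enrolled infant, so its uncharged overhead largely cancels between the RCT1 arms. Nor can the outcome-assessment visits be counted as treatment attendances, because they are made by independent assessors and their staff time is excluded as research. In RCT2 the intervention days are oral treatment at home, so only the outpatient follow-up named in Table 2 is at issue, and its frequency is not given.

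Finally, the article condenses a fuller protocol, and the hospital questionnaires are not shown. They may hold outpatient data. That bears on how easily the gap can be closed. It does not remove the mismatch between the tables and the estimation steps printed here.

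**Conclusion.** The point holds in a limited form. As written, the plan measures ward-type running costs for inpatient stays and defines nothing comparable for outpatient attendances, so the incremental cost is biased towards the intervention in both trials. The direction follows from the text, given that the costed outpatient contacts take place at the study hospitals. The article implies this by limiting staff time to hospital staff, but it does not state the place of every follow-up contact.

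The size cannot be found from the documents. Under the stated assumptions the bed-cost saving is overstated by about 1–14% in RCT1 and 0–12% in RCT2, with RCT2 probably the smaller. The saving would shrink rather than reverse. The result matters most where INB lies close to zero at a site's threshold. The disagreement between Tables 1 and 2 and the estimation text needs correcting whatever the size of the bias.

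**What to change.** 1. Keep the inpatient bed cost at nil for infants not in a bed, and add a separate outpatient overhead item per distinct facility attendance. Use outpatient-department expenditure and attendances where a hospital has them. Otherwise use a stated range of fractions of the ward running cost per bed-day, for example 0.10 and 0.25.
2. Count attendances, not the visit number V under Estimation of staff costs. V is recorded per activity and provider type, so one attendance with counselling, preparation and injection would be counted several times.
3. Report the ICER and INB with this item as a sensitivity analysis beside the planned result, by site and pooled.
4. Reconcile the operational-cost rows of Tables 1 and 2 with the Hospital data and Estimation of hospital operational costs sections: either cost administration and supervision in both arms or remove them from the tables. Treat programme support in the same way.
5. State any remaining asymmetry in Strengths and limitations.

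The cost is a small spreadsheet addition and a few sentences. The ward expenditure is already in the plan. Attendance counts may have to be derived from the treatment schedule or assumed, since data collection ended on 19 August 2024 and the article does not say that outpatient expenditure was gathered. The downside is reliance on an assumed fraction and a slightly smaller saving for the intervention.
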